## **ETHICAL CONSIDERATIONS**

### **Approval by ethics review committees**

All procedures were reviewed and approved by the Medical Ethics Committee of Yonsei University Wonju College of Medicine, Korea (YWMR-14-0-042). Written informed consent is obtained from all individual participants included in the study. All procedures are conducted in adherence with the Declaration of Helsinki and Consolidated Standards of Reporting Trials.

### **Potential risks and disadvantages**

There are a few potential risks and disadvantages for participants in the intervention group, including exercise injuries and discomfort in performing the exercise program. However, the risks and disadvantages are considered to be limited. Two experienced exercise specialists will supervise all exercise sessions at the community-based exercise medicine center operated by medical college and center. If a participant shows any signs of being physically unwell during and after an exercise session, the person will be provided a primary medical care in the hospital setting, and appropriate actions will be taken. For safety reasons, subjects who have fever ( $>38.5^\circ\text{C}$ ), infectious disease or musculoskeletal injury are not allowed to participate in the training session. If a participant reports any discomfort or incidence of injury during the intervention period, safety and further program continuation for the participant will be discussed in the research group, and in consultation with the

[figure not shown]

participant and the responsible physician. Investigators and responsible oncologists have the rights to exclude a participant from the study at any given time, if it is considered unsafe for the participant to continue. Data on adverse events will be collected systematically every week, and participants will further be informed to contact the primary investigator immediately if injuries or other adverse events related to the intervention program are required.

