| Potential risks and disadvantages | 
There are a few potential risks and disadvantages for participants in the intervention group, including exercise injuries and discomfort in performing the exercise program. However, the risks and disadvantages are considered to be limited. Two experienced exercise specialists will supervise all exercise sessions at the community-based exercise medicine center operated by medical college and center. If a participant shows any signs of being physically unwell during and after an exercise session, the person will be provided a primary medical care in the hospital setting, and appropriate actions will be taken. For safety reasons, subjects who have fever (<math>>38.5^{\circ}\text{C}</math>), infectious disease or musculoskeletal injury are not allowed to participate in the training session. If a participant reports any discomfort or incidence of injury during the intervention period, safety and further program continuation for the participant will be discussed in the research group, and in consultation with the participant and the responsible physician. Investigators and responsible oncologists have the rights to exclude a participant from the study at any given time, if it is considered unsafe for the participant to continue. Data on adverse events will be collected systematically every week, and participants will further be informed to contact the primary investigator immediately if injuries or other adverse events related to the intervention program are required.
 |

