## METHODOLOGY

### *Study design*

**Randomization** The Lifestyles Of Health And Sustainability for Breast Cancer Survivors (LOHAS-BCS) is a single-center, two-armed randomized controlled trial. Eligible participants are randomly assigned to either an exercise intervention group or a control group using sealed, computer generated random numbers with the allocation ratio of 1 to 1.

**Study procedures** Demographic characteristics are collected from personal interviews and self-reported surveys. Clinical characteristics are obtained from electrical medical records. Measurements are conducted at baseline and 12-week intervention, which include anthropometry, body composition, health-related fitness levels, and blood sample collection.

**Blinding** Four research staff members who are unaware of group assignment performed all outcome assessments. The statistician is unaware of treatment allocation until completion of the statistical analyses. Participants are not blind to their assignment but are unaware of main outcome measures, and are instructed to avoid mentioning anything regarding their study experience to the assessors.

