### **Sample size**

No prior studies have investigated the minimal clinically important difference or change in the circulating levels of WISP-1 and the  $\beta$ -catenin focusing on breast cancer patients. However, according to a previous study focusing on patients with gestational diabetes mellitus, their serum WISP-1 levels were significantly higher by 20% compared to that of healthy pregnant women. In addition, according to another calorie restriction study focusing on obese patients, the rate of clinically meaningful reduction in circulating WISP-1 level was around 27.5% in obese women. Based on results from prior studies, a 25%-point difference in the serum Wnt signaling molecule levels within each group are considered to be significant in this study. In order to detect the rate of change between baseline and 12-week intervention in both groups, and to obtain a type 1 error rate of 5% and a power of 90%, a sample size of 17 subjects per study arm are needed. To account for an expected dropout rate of ~30%, we decided to increase this number to a group size of 25. Thus, a total of 50 breast cancer survivors will be included in the study. The minimum number of subjects for adequate study power was calculated with a sample size calculator released by ClinCalc LLC. This calculator is available at <https://clincalc.com/stats/samplesize.aspx>. The formula used for power and sample size calculations is as follows:

The anticipated mean and standard deviation of group #1 =  $2104 \pm 472$  pg/mL

The anticipated percent difference in outcomes of group #2 compared to group #1 = 25%

$$k = n_2 / n_1 = 1$$

$$n_1 = (\sigma_1^2 + \sigma_2^2 / K) \times (z_{1-\alpha/2} + z_{1-\beta})^2 / \Delta^2$$

$$n_1 = (472^2 + 472^2 / 1) \times (1.96 + 1.28)^2 / 526^2$$

$$n_1 = 17$$

$$n_2 = K \times n_1 = 17$$

$$\Delta = |\mu_2 - \mu_1| = \text{absolute difference between two means}$$

$$\sigma_1, \sigma_2 = \text{variance of mean \#1 and \#2}$$

$$n_1 = \text{sample size for group \#1}$$

[figure not shown]

$n_2$  = sample size for group #2

$\alpha$  = probability of type I error (set as 0.05)

$1 - \beta$  = probability of type II error (set as 90%)

$z$  = critical Z value for a given  $\alpha$  or  $\beta$

$k$  = ratio of sample size for group #2 to group #1

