### **Data analysis**

Feasibility measures (acceptability, adherence, and adverse events etc.) are reported as numbers and percentages. Reasons for declining participation are analyzed descriptively with numbers and percentages of subjects declining for various reasons. Descriptive statistics are calculated to identify the means and standard deviations (SD) or standard errors of the mean (SEM). After Shapiro-Wilk normality test and variances analysis, parametric paired t-test or non-parametric Wilcoxon signed-rank test are used to compare the levels of health-related fitness, body composition, and serum biomarkers between before and after training, as appropriate. Pearson's and partial correlations are calculated to assess the relationships between serum levels of Wnt signaling molecules and other clinical parameters. All data are analyzed using SPSS 22.0 software (SPSS, Inc., Chicago, IL, USA). All statistical tests are two-sided and  $P$ -values less than 0.05 are considered significant.

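### Safety exclusion takes a participant out of the study without securing the 12-week assessment, so the exercise arm's before/after result may be selected towards those who tolerated training

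*Protocol*

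**What the plan says.** Four parts of the protocol bear on this point.

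- **Potential risks and disadvantages** (also in the summary table). After discomfort or injury, "safety and further program continuation for the participant will be discussed in the research group", together with the participant and the physician. The text then adds a wider power: "Investigators and responsible oncologists have the rights to exclude a participant from the study at any given time", if going on is considered unsafe for that person. The same section names exercise injury and discomfort as risks for the intervention group.
- **Study design, Study procedures.** Measurements take place at baseline and at 12 weeks, with nothing in between.
- **Data analysis.** The before/after comparisons of fitness, body composition and serum biomarkers use a paired t-test or a Wilcoxon signed-rank test.
- **Sample size.** 17 per arm are needed. "To account for an expected dropout rate of ~30%, we decided to increase this number to a group size of 25".

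Nowhere does the protocol say whether a person who stops training, or who is excluded for safety, is still seen at 12 weeks.

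**The concern.** The exclusion power is worded as removal from the study, not only from training. With a single follow-up visit, anyone who leaves before week 12 has no post-baseline value, and a paired test cannot use that person. An analysis plan written later cannot recover a blood sample that was never drawn, so the protocol is the place to secure it.

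The loss is unlikely to be balanced. Exercise injury and discomfort are risks of one arm. The Control group paragraph also offers the programme afterwards to controls who complete both tests, which may encourage controls to return. If people who tolerate training poorly also respond less well, the remaining exercise pairs look better than the arm as randomised. The fitness outcomes are the most exposed, because tolerance and result are closely linked there. WISP-1 could be affected too, though the link is less direct.

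**Working it through.** **Inputs from the protocol.** "The anticipated mean and standard deviation of group #1" is given as 2104 ± 472 pg/mL. "The anticipated percent difference in outcomes of group #2 compared to group #1 = 25" per cent, so the target is 0.25 × 2104 = 526 pg/mL. Two-sided alpha is 0.05, power 90%, allocation 1:1, dropout about 30%, and 25 per arm are enrolled.

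**Step 1: reproduce the plan's figures.**
- n = 2 × 472² × (1.96 + 1.28)² / 526² = 16.91, rounded up to 17 per arm. This matches.
- 17 / (1 − 0.30) = 24.3, rounded up to 25 per arm. This matches.
- 25 × 0.70 = 17.5, so about 17 pairs per arm remain and 7 to 8 are lost.

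The inflation keeps the number of pairs at about 17. It does nothing about which people are lost.

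**Step 2: bias formula.** If a share p of an arm is lost, the mean among those kept differs from the mean over everyone randomised by

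bias = p × (mean of those kept − mean of those lost).

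Neither p for safety exclusions nor the gap is given in the protocol, so both are assumptions. The gap is taken as 0.5 SD: 0.5 × 472 = 236 pg/mL.

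**Step 3: results for the exercise arm.**

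| Share lost selectively (assumed) | Bias, pg/mL | Share of 526 |
|---|---|---|
| 1 of 25 (4%) | 0.04 × 236 = 9.4 | 1.8% |
| 2 of 25 (8%) | 0.08 × 236 = 18.9 | 3.6% |
| 10% | 0.10 × 236 = 23.6 | 4.5% |
| 30% (all planned dropout, one arm only) | 0.30 × 236 = 70.8 | 13% |

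**Step 4: which SD.** 472 pg/mL is the SD of a level, whereas a paired test works on change. The SD of change is 472 × √(2(1 − r)), where r is the correlation between baseline and 12 weeks. The protocol does not give r.
- At r = 0.5 it is 472, and the table is unchanged.
- At r = 0.7 it is 366. Half of that is 183, so 1 to 2 of 25 give 7 to 15 pg/mL and 30% gives 55 pg/mL.

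**Step 5: what keeping everyone does to the effect and power.** Suppose those who keep training gain 526 pg/mL and a share f of the exercise arm stops and gains nothing, with all 25 per arm measured. The effect over everyone randomised is 526 × (1 − f). Power is by normal approximation with SD 472 and no baseline adjustment.

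| f | Effect, pg/mL | % of 2104 | Power at 25 per arm |
|---|---|---|---|
| 10% | 473 | 22.5% | 94% |
| 20% | 421 | 20.0% | 88% |
| 30% | 368 | 17.5% | 79% |

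If those who stop gain half the effect, f = 30% gives 447 pg/mL and 92% power.

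**The case against.** The strongest reply is that the protocol does separate the decisions. Fever, infection or injury bars a person from the training session. Continuing with the programme is discussed case by case. Only then comes a discretionary power to exclude from the study, under a safety condition and worded for any participant. A reader might infer that stopping training and leaving the study are one event, or that the exercise arm is in fact reduced to those who tolerated it. The text supports neither: someone who stops training may remain in the study and be measured. What stands is that the protocol does not secure this, and does not secure a 12-week visit for those who are excluded.

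A reader might also charge the full 30% dropout to exercise intolerance and reach 71 pg/mL, or 142 pg/mL (0.30 × 472, 27% of target) with a 1 SD gap. That does not hold. The 30% is an all-cause planning figure applied to both arms, no share of it is assigned to safety, and the protocol calls the risks limited. Paired tests also remove stable baseline differences, so the gap would have to lie in the change itself: 236 pg/mL is 45% of the whole target effect, and 472 pg/mL is 90%.

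Two further objections are accepted. Analysis sets and missing-data methods may sit in an analysis plan that is not shown, so their absence is not counted here. The lack of a named between-arm test is a separate matter, and this point does not depend on it.

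**Conclusion.** The point holds as a risk of selection, not as an established bias. It rests on three stated features taken together: exclusion from the study rather than from training alone, a single follow-up visit, and paired tests. The direction would favour exercise if those lost would have done worse.

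The size is unknown. On the assumption of 1 or 2 safety exclusions in 25 and a 0.5 SD gap, it is about 9 to 19 pg/mL for WISP-1, or 2 to 4% of the target. A figure of 71 pg/mL (13%) needs every planned dropout to be selective and confined to one arm. No comparable figure can be worked out for the fitness outcomes, because the protocol gives no SDs for them. The sample-size arithmetic is sound and is not at issue. This is a cheap improvement rather than a serious fault.

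**What to change.** Leave the clinicians' safety decision exactly as it is. In the section on potential risks and disadvantages, and in the matching summary row, add that stopping training does not by itself end follow-up. Then:

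- seek the 12-week blood draw and body measurements, already scheduled, from every randomised participant who still consents;
- leave to clinical judgement whether such a person does the fitness tests;
- compare the arms as randomised on 12-week values adjusted for baseline, with a completers analysis as sensitivity.

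Collecting the values is the main remedy. A model cannot correct loss driven by tolerance that was never measured.

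The cost is a few sentences, some effort to bring people back for one existing visit, and a somewhat diluted effect from those who stopped training. Under the no-gain assumption with all 25 per arm measured, power stays at 94% if 10% stop and falls to 79% if 30% stop.

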### ***Publication of study results***

Potentially positive, negative, or inconclusive results from the LOHAS-BCS study will be published in relevant international peer-reviewed journals. Co-authorship for the upcoming publications will be offered to members of the research group or other collaborators based on to the present work, and in accordance with the Vancouver Convention drawn up by the International Committee of Medical Journal Editors (ICMJE).

### ***Finance for the study***

The initiators of the LOHAS-BCS study are [name]. and [name], PhD. at Department of Physiology, Yonsei University Wonju College of Medicine. The LOHAS-BCS study is financially supported by a grant from the National Research Foundation of Korea funded by the Ministry of Science, ICT & Future Planning (NRF-2017R1A5A2015369) [name] is involved with. The support from the grant covers the cost of kits, reagents, materials and facilities, the partial salary of analyst for biomarker analyses. Financial support from other funding organizations will be applied, to cover expenses related to the LOHAS-BCS study. The Scientific Ethics Review Committee of the institute concerned and research members in the study will be informed about any further grants.

